## **Statistical analysis and power**

Results will be evaluated both on an intention-to-treat basis and on an as-treated (per protocol) basis. Patients who withdraw their informed consent and, thus, change their control-programme remain in their allocation group when evaluated on the intention-to-treat basis, and are excluded when evaluated on the fulfilled protocol basis. Non-randomised patients and patients withdrawing their informed consent will be analysed separately.

On the basis of the results listed in Figure 1, an estimate of 5 years' mortality at 60% and a MIREDF (Minimal Relevant Difference) of 6% seem justified. With a risk of type 1 error at 5% and type 2 error of 15%, about 1,100 patients should be randomised to each group. With an expected dropout rate of about 20%, the planned number of randomised patients should be 2,500.

Survival data will be analysed according to the Kaplan-Meier method and comparison between groups will be performed with the log-rank method. Binominal data will be analysed with Chi-square statistics and continuous data with Mann-Whitney U test.

No interim analyses are planned, as this would stop inclusion for several years.

Level of significance two-sided  $p < 0.05$ .

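### The planned 2,500 does not follow from about 1,100 per group and 20% dropout; if dropouts are lost to the analysis, log-rank power is about 80-83%, not 85%

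*Combined protocol and SAP*

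**What the plan says.** The protocol (Statistical analysis and power) takes 5-year mortality of 60% as its starting point, with "a MIREDF (Minimal Relevant Difference) of 6% seem justified". It continues: "With a risk of type 1 error at 5% and type 2 error of 15%, about 1,100 patients should be randomised to each group". The next sentence allows for losses: "With an expected dropout rate of about 20%, the planned number of randomised patients should be 2,500". The eStatistical Analysis Plan, under the same heading, repeats all of these figures unchanged.

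The protocol also states "Level of significance two-sided" 5%. It assigns the log-rank test to survival data and the chi-square test to binomial data. Patients who withdraw consent and change their follow-up programme stay in their allocated group for the intention-to-treat evaluation and are left out of the per-protocol one.

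Neither document says which arm has 60% mortality, in which direction the 6 points run, which formula gave 1,100, or what counts as dropout.

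**The concern.** The three numbers in the sample size statement do not fit together. Anyone who applies the stated dropout to the stated requirement gets a total that differs from the planned one by 250 patients, which is 10% of the plan.

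What is at stake is how a result that misses significance is read. The later 10-year analysis plan (section 1, Study design) describes the trial's findings as not fully conclusive while pointing to a small difference that may matter. In that setting readers lean on the declared type 2 error to judge how firmly a 6-point difference has been excluded. If the declared error is lower than the plan's own inputs support, they will exclude it too firmly.

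**Working it through.** **Inputs, all from Statistical analysis and power:** two-sided 5% (z = 1.960); power 85% (z = 1.036); mortality 60%; difference 6 points, read as absolute (a relative 6% would need more than 3,000 per group); 1,100 per group; dropout 20%; total 2,500. As the direction is not given, 60 vs 54, 60 vs 66 and 63 vs 57 were all tried.

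**1. Reproduce 1,100 per group.** Log-rank (Schoenfeld): HR = ln(1-p2)/ln(1-p1); events D = 4(1.960 + 1.036)²/(ln HR)²; n per group = D/(p1 + p2).

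| Contrast | HR | Events | n per group |
|---|---|---|---|
| 60 vs 54 | 0.847 | 1,312 | 1,151 |
| 63 vs 57 | 0.849 | 1,338 | 1,115 |
| 60 vs 66 | 1.177 | 1,348 | 1,070 |

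So 1,100 is consistent with a log-rank calculation. The two-proportion formula gives 1,162 (60 vs 66) to 1,222 (60 vs 54) and does not reproduce it.

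**2. Try to reproduce 2,500.**
- 2,200/(1 - 0.20) = 2,750, which is 1,375 per group.
- The cruder 2,200 × 1.20 = 2,640.
- Dropout that 2,500 does cover: 1 - 2,200/2,500 = 12%.
- Patients left from 2,500 after 20% loss: 2,500 × 0.80 = 2,000, or 1,000 per group.

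**3. Power with 1,000 per group, dropouts wholly lost.** Log-rank power = Φ(½√D × |ln HR| - 1.960).
- 60 vs 54: D = 1,000 × 1.14 = 1,140; ½ × 33.76 × 0.1655 - 1.960 = 0.834; power 79.8%.
- 60 vs 66: D = 1,000 × 1.26 = 1,260; ½ × 35.50 × 0.1633 - 1.960 = 0.938; power 82.6%.
- Scaling the plan's own 85% at 1,100: (1.960 + 1.036) × √(1,000/1,100) - 1.960 = 0.897; power 81.5%.

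**4. Chi-square on 5-year proportions, for comparison** (pooled variance).

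| n per group | 60 vs 54 | 60 vs 66 |
|---|---|---|
| 1,100 | 81.2% | 83.1% |
| 1,000 | 77.4% | 79.4% |

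**5. What 2,500 does support under log-rank.**
- Difference detectable with 85% power at 1,000 per group, found by solving the formula in step 3 for p2: about 6.4 points below 60% or 6.2 points above it.
- Dropout at which 85% power for 6 points still holds: 1 - 1,151/1,250 = 8% (60 vs 54) to 1 - 1,070/1,250 = 14% (60 vs 66).

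**6. If dropouts stay in the intention-to-treat set with full mortality data (1,250 per group).**
- Undiluted effect: 1,425 or 1,575 events; log-rank power 87.8% to 90.0%.
- Difference diluted to 0.8 × 6 = 4.8 points (assumption: the 20% gain no contrast): 60 vs 55.2 gives 70.7%; 60 vs 64.8 gives 73.2%.

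**The case against.** The best defence is that a shortfall in power appears only if every dropout contributes nothing. The protocol keeps consent withdrawals in their allocated group, and a log-rank analysis uses follow-up up to censoring. If dropouts still yield 90% of all expected events (an assumption), log-rank power at 1,250 per group is about 84-87%. With complete mortality data and an undiluted effect it is 88-90%. This stands: a reader might infer that the design simply lacks 85% power, and the documents do not support that as an unconditional statement. But the defence does not rescue the figures. On that reading no inflation for dropout was needed, yet the plan makes one. The plan also says that withdrawing patients change programme, so an undiluted effect is not assured.

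A reader might also infer that the uncovered dropout pulls power down to 77%. It does not. That figure belongs to a chi-square comparison, which has only 81-83% power at 1,100 per group before any loss. The plan names log-rank for survival data. On the plan's own basis the shortfall costs about 3.5 points (85% to 81.5%).

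Two other defences fail. A one-sided calculation for 60 vs 54 gives totals of 2,445 to 2,528 after inflation, but it contradicts both the two-sided level and the stated 1,100. And the word for approximation in the plan does not stretch to a gap of 250 patients.

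**Conclusion.** The sample size statement is wrong as written in both documents: 1,100 per group, 20% dropout and 2,500 cannot all hold. That part is plain division and needs no assumption.

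The consequence for power is conditional. If dropouts are lost to the analysis, the type 2 error for a 6-point difference is about 17-20% under log-rank, against the stated 15%. The spread comes from the undeclared direction of the difference. Depending on what dropout means, log-rank power at 2,500 could lie anywhere from about 71% to 90%, and the plan gives no basis for choosing within that range. This is a modest misstatement of a design property that readers rely on. It does not threaten the validity of the comparison itself.

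**What to change.** Keep 2,500 and restate the paragraph in the protocol and in the eStatistical Analysis Plan, for example:

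> 2,500 patients randomised. With 20% lost to the analysis, about 1,000 per group remain, giving about 80-83% power (log-rank, two-sided 5%) for a 6-point difference from 60% mortality, or 85% power for a difference of about 6.2-6.4 points. Power of 85% for 6 points holds only if dropout is about 8-14%, depending on the direction of the difference.

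Add that these figures treat dropouts as lost. If they stay in the intention-to-treat analysis with full mortality data, power at 1,250 per group is about 88-90% with an undiluted effect, and about 71-73% if the difference dilutes to 4.8 points (assumption). State the formula, which arm has 60%, the direction of the 6 points, and the definition of dropout; once the direction is fixed, each range narrows to one figure. If a chi-square comparison of 5-year proportions is also to be reported, give its power separately (about 77-79% at 1,000 per group).

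The cost is wording in two documents. There are no extra patients and no change to endpoint, test or analysis set. The one drawback is a slightly less favourable stated power.

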## **Ethical considerations**

The meta-analyses provide no reason for a firm conclusion on the effectiveness of specific follow-up programmes, although arguably the studies “consistently” suggest that more follow-up (of some sort) is better than no follow-up at all. The question is how often patients have to be checked. Community equipoise exists due to the uncertainty of the regimens. There might be problems with patients' and doctors' equipoise, as patients report a strong preference for pre-scheduled follow-up (Stiggelbout *et al.*, 1997), but the opposite feelings also exist among patients. In a similar investigation among patients with breast cancer, 66.5% of the women accepted randomisation into follow-up in the primary or hospital sector.

Patients in the intervention group might appear to be offered more intense treatment. It is doubtful whether this is of benefit for the individual patient, considering the psychological stress the intensive follow-up programme and the possible side effects of extra therapy will imply for the patient.

Patients refusing to participate will be followed according to the individual departments' local guidelines. Patients who refuse to participate are followed in the database. Consent for this is not needed, as this is a part of the general record keeping.

All participants must give informed consent for participation. This can be withdrawn at any time.

The demands in the Declaration of Helsinki are met.

## **Organisation**

The study will be undertaken under the auspices of a steering committee elected among the persons in the study group. The steering group should consist of preferable 2 persons from each participating country. The monitoring groups will be appointed among people not directly involved in the investigation.

Centres will be recruited from all over Denmark, Sweden, Poland and Uruguay. Due to the patients' preference for pre-scheduled follow-up, a low recruitment rate can be expected. Each centre should be able to recruit at least 50 patients within two years. This requires at least 50 participating centres.

Each centre will appoint a principal investigator who will be responsible for local administration and recruitment of diagnostic departments (Radiology, Nuclear Medicine, Ultrasound departments). Each country appoints a monitoring committee, and a committee for evaluation of patients suspected of recurrence. Each centre is recommended to appoint a study nurse for running the study.

A central secretariat will be placed in a suitable institution (pt at Cochrane Colorectal Cancer Group at Bispebjerg Hospital, Copenhagen, Denmark) and is staffed with a full-time secretary and preferably with a half-time academic employee. The secretariat will collect a log of all included patients, monitor the individual centres for inclusion of eligible patients on a daily basis, and serve as the central allocation unit. If a centre does not recruit at least 30% of eligible patients, the centre should be withdrawn from the study.

## **Economics**

No industrial sponsors can be expected to volunteer in this project. Funds will be sought from private and official funds in the participating countries. Funds from the EU will also be considered. The central steering group will support applications for local support.

If economically feasible each included patient should be reimbursed with 125 EUROS to be given to the individual department. Total expense is estimated to be 375,000 EUROS.

Centres will cover their own expenses for the diagnostic tests.

Organisational expenses are also expected for the secretariat and data handling unit (estimated at 100,000 EUROS/year), for travel and meeting expenses, for local monitoring and secondary treatment groups (estimated at 150,000 EUROS/the whole study). Expenses for the diagnostic investigations and study-nurses in the individual centres are to be met directly by the centres. With

2 years of recruitment and 5 years of follow-up, the total requirement for funds will be about 1,250,000 EUROS.

The Nordic Cancer Union was sought for grants for starting and detailed planning of the study by May 15, 2003; 25.000 EUROS were allowed to cover the planning phase and a feasibility pilot study.

The Danish Cancer Society has granted 800.000 dkr. for use in 2007/2008. And the Danish Agency for Science, Technology and Innovation donated 1.082.550 dkr. to be used in 2008-2010.

### **Side-protocols**

Such are allowed in the respect that they do not interfere with the main project. At this stage, the following side-protocols are planned:

- Cost effectiveness-analyses stratified for each participating country;
- Sampling of blood and tissue for risk-factor analysis;
- Quality of life for included patients
- Observational study of survival and risk factors after salvage surgery for recurrence.

Private companies might be involved in some local side-protocols. This could create conflict of interests. Local projects on COLOFOL patients will be performed with no responsibility from the steering group, but will have to be approved by the steering group, ensuring no interference with the main project occurs. The side-protocols have to develop their own patient information and ethical considerations.

### **Time schedule**

2003-4: Planning, fund-raising, final protocol, case record forms, ethical committees, recruitment of centres, feasibility studies.  
2005-8: Inclusion of patients  
2013: Last patient followed-up for 5 years.

### **Publication**

The Steering Group will appoint a writing committee to report the results on behalf of the COLOFOL-group. All investigators will be eligible. All investigators will be listed by name at the end of the presenting paper.

### **Amendments to the original protocol decided by the steering group after initiation of trial:**

Regarding **Data collection**:

The initial request of the reporting of all non-included eligible patients proved difficult to insure in all participating centers, so a comparison of study and source population will be explored in a separate paper.

The Quality of life measurement will be conducted as a side protocol and reported as a separate paper.

The Cost effectiveness will be reported as a separate paper.

### Regarding **Efficacy parameters**:

As evidence suggested that the 3 year effect-parameter of total mortality and cancer-specific mortality to be an excellent surrogate to 5 years, the steering decided in September 2012 to publish both 3 and 5 years total mortality and cancer-specific mortality, along with the secondary endpoint of recurrence-free survival.

### Regarding **Organisation**:

The initial requirement that If a centre does not recruit at least 30% of eligible patients, the centre should be withdrawn from the study and that each centre should be able to recruit at least 50 patients within two years, were explicitly based on at least 50 participating centres. Despite continues effort neither the UK, Holland nor Hungary will be participating, so an adjustment is needed to achieve the planned number of randomised patients. The Steering Group decided in September 2010 to impose cut-of off >20 included patients to insure quality of the management at the participating department in Denmark, Ireland, Poland, Sweden and Uruguay.

### Regarding **Time schedule**:

The schedule will adjusted according to the prolonged inclusion period, so that inclusion are to be completed by the end of 2010 and the completion of the last patient follow-up for 5 years by the end 2015/early 2016.

## **Appendix 1 A**

### **COLOFOL**

#### **Common side protocol**

#### **Bank of blood and tissue samples**

##### **Blood samples**

Three samples of 10 ml peripheral blood are collected preoperatively prior to any neoadjuvant chemotherapy and/or radiotherapy. 10 ml is drawn in one EDTA tube, 10 ml in one heparinized tube, and 10 ml in one serum tube.

Samples are pinned for 15 minutes at 1500G within 30 minutes after collection.

The pinned EDTA tube and the pinned heparinized tube samples are split into 10 fractions: 3 x 1.6 ml plasma, 1 x 1.6 ml buffy coat, and 1 x 1.6 ml erythrocyte fraction.

The pinned plasma tube sample is split into 3 x 1.6 ml. Altogether 13 fractions collected in cryotubes are present after the separation.

The 13 cryotubes are immediately frozen at  $-80^{\circ}\text{C}$  until analysis.

##### **Tissue samples**

If possible due to the tumour size, four biopsies each measuring appr.  $0.5 \times 0.5 \times 0.5$  cm are cut from the fresh, unfixed tumour immediately after the specimen has been resected. The biopsies are stored in cryotubes marked T1, T2, T3, T4 (tumour).

A biopsy of at least  $0.5 \times 0.5$  cm is cut from the macroscopically normal mucosa appr. 10 cm from the tumour. The normal biopsy is put in a cryotube marked N (normal).

All tissue samples should be snapfrozen, and stored at  $-80^{\circ}\text{C}$  until analysis.

##### **Storage**

Blood and serum samples are stored at each investigational center until analysis.

As a general agreement, all samples are available for COLOFOL research projects after approval of the COLOFOL Steering group.

## APPENDIX 1 B

### COLOFOL

#### Guidelines

#### Liver CT

Patient position: Supine  
Oral contrast material: Water  
Breath-hold: One single breath-hold in each phase in maximum inspiration

The values in the protocol are recommended parameters.

#### PROTOCOL

| PROTOCOL            | BEFORE CONTRAST                   | AFTER CONTRAST         |                        |                        |
|---------------------|-----------------------------------|------------------------|------------------------|------------------------|
|                     |                                   | SINGLE-SLICE           | 4 - SLICE              | 16 - SLICE             |
| SCAN COVERAGE       | liver                             | liver                  | liver                  | liver                  |
| COLLIMATION         | same parameters as after contrast | 5mm                    | 4x2,5                  | 16x1,5                 |
| PITCH               |                                   |                        | 1,25                   | 1,5                    |
| ROTATION TIME (sec) |                                   | 1                      | 0.75                   | 0.75                   |
| kV                  |                                   | 130                    | 120                    | 120                    |
| mAs                 |                                   | 180                    | 180                    | 200                    |
| Matrix min/filter   |                                   | 512/B                  | 512/B                  | 512/B                  |
| IV-kontrast  |                                   |                        |                        |                        |
| Concentration       |                                   | 300 mg I / ml          | 300 mg I / ml          | 300 mg I / ml          |
| Volume              |                                   | 2 ml / kg (max 180 ml) | 2 ml / kg (max 180 ml) | 2 ml / kg (max 180 ml) |
| Flow                |                                   | 4 ml/sec               | 4 ml/sec               | 4 ml/sec               |
| Scan delay          |                                   | 50 sec                 | 65 sec                 | 70 sec                 |
| Preparation         | 2 glasses of water                | 2 glasses of water     | 2 glasses of water     | 2 glasses of water     |

#### Post-processing

The images should be evaluated with different W/L settings. Especially specific liver window settings are recommended for evaluation.

After the baseline scanning all parameters have to be constant in subsequent control examinations.

## APPENDIX 1 C

### COLOFOL

#### Guidelines

#### Liver and abdominal CT

Patient position: Supine  
Oral contrast material: Barium – or iodic contrast material (abdomen) and water (liver)  
Breath-hold: One single breath-hold in each phase in maximum inspiration

The values in the protocol are recommended parameters.

#### PROTOCOL

| PROTOCOL            | BEFORE CONTRAST                      | AFTER CONTRAST         |                        |                        |
|---------------------|--------------------------------------|------------------------|------------------------|------------------------|
|                     |                                      | SINGLE-SLICE           | 4 - SLICE              | 16 - SLICE             |
|                     |                                      |                        |                        |                        |
| SCAN COVERAGE       | liver                                | Liver + abdomen        | Liver + abdomen        | Liver + abdomen        |
| COLLIMATION         | same parameters as
after contrast | 5mm                    | 4x2,5                  | 16x1,5                 |
| PITCH               |                                      |                        | 1,25                   | 1,5                    |
| ROTATION TIME (sec) |                                      | 1                      | 0.75                   | 0.75                   |
| kV                  |                                      | 130                    | 120                    | 120                    |
| mAs                 |                                      | 180                    | 180                    | 200                    |
| Matrix/filter       |                                      | 512/B                  | 512/B                  | 512/B                  |
| IV-kontrast  |                                      |                        |                        |                        |
| Concentration       |                                      | 300 mg I / ml          | 300 mg I / ml          | 300 mg I / ml          |
| Volume              |                                      | 2 ml / kg (max 180 ml) | 2 ml / kg (max 180 ml) | 2 ml / kg (max 180 ml) |
| Flow                |                                      | 4 ml/sec               | 4 ml/sec               | 4 ml/sec               |
| Scan delay          |                                      | 50 sec                 | 65 sec                 | 70 sec                 |
| Preparation         | 2 glasses of water                   | 2 glasses of water     | 2 glasses of water     | 2 glasses of water     |

#### Post-processing

The images should be evaluated with different W/L settings. Especially specific liver window settings are recommended for evaluation.

After the baseline scanning all parameters have to be constant in subsequent control examinations.

[figure not shown]

A = Thorax  
B = Liver  
C = Liver/abdomen

## APPENDIX 1 D

### COLOFOL

#### Guidelines

#### CT-Chest – low dose

Patient position: Supine  
Oral contrast material: -  
Breath-hold: One single breath-hold in each phase in maximum inspiration

The values in the protocol are recommended parameters.

